### 2.8. Ethics and Dissemination

The study has been awarded ethical approval from the committee of the Universidad Católica San Antonia de Murcia (CE032213).

## 3. Expected Results

Personalized FO along with a specific exercise regimen are expected to produce better results for signs and symptoms of PFF compared to specific exercises alone. In addition, it will be detected if the possible bias that has made the previous studies not demonstrate the efficacy of FO is that these FO were not personalized.

After the completion of this study, in which a large number of tests will be analyzed, the research will provide a definition of the PFF according to the common findings presented by the sample, a definition that nowadays is non-existent. Finally, we can evaluate if there is a correlation between clinical methods and the diagnosis and severity of PFF, in order to make an accurate diagnosis.

It is anticipated that the study will provide valuable evidence for improvement of the treatment of PFF, as well as for the diagnosis and management of this entity.

The main future research which is required after this protocol study is to carry out the detailed RCT described in the present manuscript. Also, qualitative research to understand the experience of patients with PFF wearing an FO is required.

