Therefore, the objective of the current study is to design a protocol for a randomized controlled trial (RCT) to determine whether personalized FO together with a specific exercise regimen produce the same or better results regarding the signs and symptoms of PFF, compared to only specific exercises. In addition, as specific objectives, to detect whether the possible bias that has prevented previous studies from demonstrating the efficacy of FO is due to the fact that these FO were not personalized; to define the PFF and to evaluate if there is a correlation between the clinical methods and the diagnosis and severity of the PFF.

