## 2. Materials and Methods

### 2.1. Study Design and Setting

The design is a randomized controlled two-arm trial.

Patients will be recruited from the university clinic from Universidad Católica San Antonio de Murcia, University of Malaga and schools nearby in Spain. They will be randomized to one of the two groups, each receiving a different intervention. The schedule to follow while carrying out this RCT can be found in Appendix A. The total period intended to be allocated to this study is from September 2023 to February 2025.

To randomize the sample, a Microsoft Excel spreadsheet will be used where a random assignment sequence will be generated. Each patient will be given a consecutive number in order of arrival and allocation concealed in envelopes.

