### 2.3. Interventions

At the first visit, parents will be informed of their child’s current problem, treatments, and the existence of this study. In the case of accepting to participate in the study, the process will begin: all the variables will be carefully collected, the treatment will be established and an appointment will be made for follow-up at 6 months.

First, all the affiliation data will be collected and the PFF will be diagnosed.

#### 2.3.1. Group 1

For custom insoles, a mold will be taken using phenolic foam. To do this, the child will be asked to sit in a chair (to take the mold semi-load baring). The mold will be taken in a corrected position, that is, limiting the internal rotation of the tibia with one hand and the windlass mechanism will be performed to increase the MLA. The mold must remain neutral, so in the event that a varus or valgus print has emerged, this process will be repeated. Once we have the mold filled with plaster, two modifications will be made: a moderate medial heel skive (5 mm and an angulation of 15°) in the hindfoot and a slight inversion balance of 4° in the forefoot. Once the mold is prepared, the FO will be thermoformed; for this, we will use a 3 mm polypropylene, 25 Shore-A EVA as lining and 65 Shore-A EVA to stabilize the hindfoot.

In addition, the exercises to be performed will be explained to them and they will be given all the recommendations regarding the performance of exercises, the use of FOs and shoe therapy. These explanations will be provided in an additional report (Appendix C) that will be given to all subjects together with a calendar so that they write down all the days they perform the exercises with an X.

The exercises will first be explained by the podiatrist to the child and the parent/legal guardian. In addition, a standard video will be created so that the child can see it, in which the exercises will be explained through drawings in order to capture the attention of the child. The parent/legal guardian needs to confirm that the child is doing it correctly.

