Once the FO have been provided, after assessing that it adapts well to the foot and does not cause discomfort, the patient will be requested to come in at 6 months. In the event that there is any discomfort or irritation to the child’s skin, an appointment will be made to readjust or modify the FO (in this visit the variables will not be evaluated, only the FO will be fixed; if there are no problems, this visit will not be carried out).

#### 2.3.2. Group 2

The participants will have the same intervention described for group 1, with the difference that they will use a placebo FO. This will be constructed using flat 1 mm 65 shore Ethylene-vinyl acetate (EVA), which will be cut to the foot size of the child and covered with the same top cover as the FO Group 1 to visually prevent them from being distinguished.

The instruments necessary for the development of this study and the budget necessary to carry out this clinical trial are included in Appendix D.

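### The two-arm design cannot show whether lack of personalisation explains earlier negative orthosis studies, although sections 1 and 3 promise that it will

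*Protocol article*

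**What the plan says.** Section 1 (Introduction) names a main objective and then three specific ones: a question about personalisation, a definition of pediatric flat foot, and the correlation of clinical methods with diagnosis and severity. The first of these asks whether the suspected bias in earlier studies "is due to the fact that these FO were not personalized". Section 3 (Expected Results) turns this into a promised finding: "it will be detected if the possible bias that has made the previous studies not demonstrate the efficacy of FO" lies in a lack of personalisation.

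The design is given in sections 2.1 and 2.3:

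- Arms: "The design is a randomized controlled two-arm trial".
- Group 1: "For custom insoles, a mold will be taken using phenolic foam". The mould then receives two fixed modifications, and the child also gets the exercise programme.
- Group 2: the same intervention, "with the difference that they will use a placebo FO". On that placebo device: "This will be constructed using flat 1 mm 65 shore Ethylene-vinyl acetate (EVA), which will be cut to the foot size of the child".

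Section 2.7 plans a between-group test of control against experimental group and names no other group comparison. The limitations in section 3.1 mention the lack of an untreated group, but not the lack of a non-personalised corrective orthosis.

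**The concern.** Whether personalisation matters is a question about two corrective devices, one made for the child and one not. This trial contrasts a corrective device with a placebo. The group difference therefore combines whatever any corrective orthosis does with whatever personalisation adds.

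What is at stake is a conclusion in the final report. A favourable result could be presented as showing that earlier studies were negative because their devices were not custom made. That statement would bear on how other trials are read and on whether custom devices are needed, and no randomised comparison would stand behind it.

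**Working it through.** The article gives no figure for this objective, so the check sets the objective against the allocation and asks what the contrast identifies.

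**1. Who receives what** (sections 2.3.1, 2.3.2 and 2.6)

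| Device, all with the same exercises | Children planned |
|---|---|
| Custom corrective orthosis | 84 |
| Flat 1 mm placebo insole | 84 |
| Corrective orthosis, not personalised | 168 − 84 − 84 = 0 |

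**2. What the contrast estimates.** Let C, N and P be the mean outcomes under a custom corrective orthosis, a non-personalised corrective orthosis and the placebo, each with exercises. Then

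C − P = (C − N) + (N − P).

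The trial estimates the left side. The objective concerns C − N. N is never observed, so there is one equation with two unknowns. If the trial found C − P = D, then C − N = D with N − P = 0 (only personalisation works) fits exactly as well as C − N = 0 with N − P = D (any corrective orthosis works). A larger sample makes D more precise but does not split it.

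**3. Could other information in the trial supply N?**

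- *Previously treated children:* excluded by section 2.2, so there is no internal record of earlier devices.
- *Variation within Group 1:* sections 2.3.1 and 2.5 allow a device to be readjusted for an individual child. Such changes follow poor adaptation, are not randomised, and are made to a device that is already custom.
- *The placebo:* it is cut to the child's foot size, but it is flat and the article calls it a placebo. It stands for P, not N.
- *Materials:* Appendix D lists moulding and fabrication materials and no prefabricated device.

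**4. Positive result.** Beyond the ambiguity in step 2, section 1 says the study will differ from earlier work in sample size, length of follow-up and use of a standardised diagnostic protocol. Any of these could make its result differ from an earlier negative one.

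**5. Null result.** Suppose C − P is truly zero, children wore the devices, and neither term on the right side is negative. Then both terms are zero, and personalisation did not rescue efficacy. That counts against the personalisation explanation, but it does not say what did cause the earlier negative findings.

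**The case against.** The strongest reply is that the objective is about earlier studies, so comparison with outside evidence is inherent in it. If those studies showed N − P near zero and this trial shows C − P above zero, the difference points to personalisation. The argument is coherent, but it needs the earlier N − P to carry over to this trial's children, diagnosis and follow-up, and section 1 itself stresses differences on those points. The article describes no such indirect comparison and does not sort the cited studies by type of device. It would support a discussion paragraph, not a promise of detection.

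A second reply is that this is a secondary aim, hedged by the word possible, and correctable at reporting. The first part stands and limits the severity. The hedge applies to the bias, however, and not to the promise in section 3 that the trial will settle the matter.

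Nor can the point be left to an analysis plan: the arms are fixed in the article, and no analysis can create the missing comparator.

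A reader might also infer two stronger things that the documents do not support:

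- *That the trial says nothing at all about personalisation, whatever it finds.* Step 5 of the working shows that a null result with adequate wear is partly informative.
- *That the missing arm leaves a null result open to poor wear.* That ambiguity is about adherence. A further arm would not remove it, and section 3.1 already discloses it.

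**Conclusion.** The concern holds as a mismatch between one stated objective and the stated design. The trial has no randomised contrast between personalised and non-personalised corrective orthoses, with 0 of 168 children in the second category. It therefore cannot attribute an effect to personalisation or explain earlier negative studies. A null result could weaken the personalisation explanation and do no more.

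The size is limited: one of three specific objectives and its echo in section 3. It would be tempting to read this as a flaw in the trial as a whole, but the documents do not support that. Randomisation, arms, outcomes and the test of experimental against control group are untouched. This should be fixed, but it does not stand in the way of the main comparison.

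The conclusion rests on the device descriptions in section 2.3 being complete as to arms. It does not depend on which devices the earlier studies used, which the documents do not show.

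**What to change.** 1. In section 1, delete the personalisation objective. In section 3, delete the matching sentence. Alternatively, recast both as a hypothesis to be taken up in non-randomised discussion of earlier studies.
2. In section 3.1, add a line such as: *Because no group receives a non-personalised corrective orthosis, the trial cannot attribute any effect to personalisation or explain why earlier studies were negative.*

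No replacement objective is needed. The main objective, as the Abstract and section 2.3 set it up, already covers the personalised orthosis against the placebo orthosis with the same exercises in both groups.

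The cost is wording only. Arms, sample size, treatment and analysis stay as they are, and the trial gives up one secondary claim.

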## 1. Introduction

Pediatric flat foot (PFF) is a very frequent syndrome in primary care consultations, and it is also a shared concern among parents and professionals. Currently, there is no clear definition for the diagnosis of PFF, no treatment protocol, nor solid scientific evidence on the wide range of treatments [1,2].

PFF is characterized by a talocalcaneal misalignment, which is reflected as a collapse of the medial longitudinal arch (MLA) in a standing position [3]. Consequently, there is excessive pronation, accompanied by a drooping of the navicular. Some feet are also accompanied by calcaneal valgus [4]. All these alterations in the morphology of the foot force the rest of the structures, such as soft tissues or joints, to compensate for the excessive forces that act on the MLA [5]. These compensations cause an inefficient gait and symptoms such as pain, fatigue, stumbling when walking, problems in the proximal joints and reduced quality of life [6,7].

Diagnosis is based on clinical findings, including a variety of clinical tests and radiographic signs, these being considered the “gold standard” [6,8,9].

Regarding treatment, there are both conservative and surgical options, surgical being the last treatment option [10]. The most common conservative treatment is the use of foot orthoses (FO), where previous studies have concluded that they improve the results of some clinical tests, radiographic angles and symptomatology [11,12,13,14,15,16,17]. The purpose of the FO is to modify the position of the axis of the subtalar joint, decrease the speed of pronation, support the MLA and distribute loads more effectively [18,19]. Previous systematic reviews indicate that FO are beneficial and create positive changes in the development of the child’s foot [8,20,21]; these changes being greater in earlier ages of the treatment [22]. The exact age to start treatment is not clear, although it is recommended to start at preschool age (under 7 years old) so that the possibility of correcting the PFF is greater [23,24]. It has also been seen that the combination of FO with exercises is much more beneficial [25]. However, other studies indicate that the modifications that occur are those resulting from the natural development of the foot [26,27]. The evidence regarding the use of FO still does not present a consensus [20,28,29].

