### 2.2. Eligibility Criteria

Subjects aged 3 to 12 years diagnosed with PFF. For the diagnosis of the PFF, the following criteria must be met:Foot Posture Index (FPI) > 6 [33].Navicular drop > 10 mm [34].Relaxed calcaneal stance position (RCSP) 6° to 12° valgus [35].Pronation angle > 10° [36].Arch index > a 1.35 [37].Double/single heel rise test negative [38].Windlass test negative [39].

In addition, the signature of the parents or legal guardians with consent to participate in the study will be necessary (Appendix B).

Participants will be excluded if they have undergone any surgery in the lower limbs, have previously received treatment for PFF, present osteoarticular injury, foot fractures or in the lower limbs in the last 6 months, ankle sprain, asymmetry, systemic diseases with osteoarticular involvement that present symptoms in the lower limb with gait disturbance (for example, Perthes disease) or biomechanical alteration of the lower limb with repercussions on the foot and ankle. Children suffering from any type of neurological or systemic disability (cerebral palsy, Down Syndrome, clubfoot or equino-varus, …) will also be excluded.

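### With only children who already meet the PFF entry criteria, the trial cannot correlate tests with the diagnosis or derive a definition that distinguishes PFF

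*Protocol article*

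**What the plan says.** Section 2.2 of the protocol article admits "Subjects aged 3 to 12 years diagnosed with PFF" and continues: "For the diagnosis of the PFF, the following criteria must be met". Seven items follow: FPI above 6, navicular drop above 10 mm, "Relaxed calcaneal stance position (RCSP) 6° to 12° valgus [35", pronation angle above 10°, an arch index limit, and a required result on the heel rise and windlass tests. Nothing says that any one of them, or some number out of seven, is enough.

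Sections 2.1 and 2.3 place these children in two randomized arms. Section 2.3 collects the variables once the family has agreed to take part. No neutral-foot group is described, and no data set of children who were examined and not enrolled.

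The last paragraph of section 1 lists three specific objectives. Two concern diagnosis: to define PFF, and "to evaluate if there is a correlation between the clinical methods and the diagnosis and severity of the PFF". Section 3 states the expected product: "the research will provide a definition of the PFF according to the common findings presented by the sample". It adds that the correlation will serve accurate diagnosis. Section 2.7 names the methods: regression or Pearson correlation, chi-square, and Student's t or ANOVA, with rank-based alternatives.

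**The concern.** To say which findings define a condition, or how a test relates to its diagnosis, a study needs people with and without the condition. This trial has only the first group, and selects it by several of the same tests that are to be evaluated.

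The stake is what the final report may claim. Section 3 presents the definition as something that does not yet exist. If the report lists the findings common in its sample, a reader may take the investigators' own entry rule for an empirical result. A sign that is common in all children of this age may likewise pass for a sign of PFF. Two of the three specific objectives are touched: the definition wholly, and the correlation objective in its diagnosis part.

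**Working it through.** The plan gives no figure of its own on this point, so there is none to reproduce. The check sets the entry rule against each promised result.

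**1. Correlation with the diagnosis.** Let D = 1 if a child has PFF. Section 2.2 makes D = 1 for every enrolled child, 168 by section 2.6. Then Var(D) = 0, and for any test X, r = Cov(X, D) / √(Var(X)·Var(D)) = 0/0, which is undefined. The other methods of section 2.7 fail in the same way: chi-square has a single diagnosis column, and t or ANOVA has one group.

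**2. Definition from common findings.**
- *The seven criterion tests.* Each is held at, or within, its entry limit in every child. Tabulating what is common returns the entry limits.
- *The other tests* in sections 2.4.1 and 2.4.2, for example Beighton scale, supination resistance, Chippaux-Smirak index and navicular height. Entry does not fix these directly, so their frequencies are real information about the sample. To distinguish PFF, a finding F needs P(F | PFF) compared with P(F | no PFF). The trial estimates only the first.

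**3. Severity and associations among tests.** These can be estimated. FPI above 6 still spans the two upper categories of section 2.4.1 (pronated, to +9; highly pronated, +10 to +12), and navicular drop and pronation angle have no upper limit. Selection narrows the range, however. The article does not say where the cut-offs fall among unselected children, so the percentiles below are assumptions, with a bivariate normal distribution.

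*Both tests are entry criteria, both above the same percentile* (simulation, 6 million pairs):

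| True r | Cut at 50th | Cut at 80th |
|---|---|---|
| 0.6 | 0.36 | 0.26 |
| 0.8 | 0.60 | 0.49 |

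*Only one of the two tests is an entry criterion.* With cut-off z at percentile q, λ = φ(z)/(1 − q), v = 1 + zλ − λ², and r′ = ρ√v / √(1 − ρ² + ρ²v).
- 50th: z = 0, λ = 0.798, v = 0.363, √v = 0.603. For ρ = 0.6, r′ = 0.362/√(0.640 + 0.131) = 0.41. For ρ = 0.8, r′ = 0.482/√(0.360 + 0.233) = 0.63.
- 80th: z = 0.842, λ = 1.400, v = 0.219, √v = 0.468. For ρ = 0.6, r′ = 0.281/√(0.640 + 0.079) = 0.33. For ρ = 0.8, r′ = 0.374/√(0.360 + 0.140) = 0.53.

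The attenuation is present throughout, and is smaller when only one test is selected on. RCSP is bounded on both sides at entry, which narrows its range further.

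**The case against.** Four arguments for the plan deserve weight.

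*The definition is to rest on many tests, not only the seven.* This is true, and a reader who inferred that the whole definition is circular would go too far. Circularity is strict only for the criterion tests. For the rest, the problem is the missing comparison with children without PFF.

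*Severity varies, and four assessments are planned (section 2.5).* This also stands. It would be wrong to say that selection fixes the severity part of the objective. At later visits some children may cease to meet the criteria, but their status would still be set by the same tests, and the article plans no such analysis. That the article names no severity measure is not held against it, since a condensed article may leave this to the full protocol.

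*The article never promises specificity and need not take radiographs.* Agreed. Section 1 describes diagnosis as based on clinical findings, "including a variety of clinical tests and radiographic signs", and its remark on the reference standard can be read as covering both kinds. Not collecting radiographs is a design choice and no part of this point.

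*These are secondary aims.* They are, and that limits the weight of the point. It does not make an undefined correlation estimable.

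One more inference should be avoided: that each of the seven signs is present in 100% of the sample. Section 2.2 asks for "Arch index > a 1.35 [37].Double/single heel rise test negative [38].Windlass test negative [39", whereas section 2.4.1 scores the heel rise and windlass tests positive when the response is abnormal. Section 2.4.2 also defines the arch index as B/(A + B + C), which cannot exceed 1. These passages must be reconciled. The present argument needs only that entry fixes or restricts the criterion tests, whichever way they are scored.

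**Conclusion.** The concern holds in this form. At baseline the correlation of any test with the diagnosis is undefined. A definition from the sample's common findings restates entry for the seven criterion tests, and for the others cannot show what sets PFF apart. Both conclusions follow from the entry rule and the absence of children without PFF. They need no distributional assumption, and no analysis plan could repair them from the enrolled children's baseline data.

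Associations among tests and with severity survive in attenuated form. The size rests on assumed cut-off percentiles and normality: with both tests selected on, a true 0.6 appears as about 0.36 to 0.26 and a true 0.8 as about 0.60 to 0.49; with one selected on, about 0.41 to 0.33 and 0.63 to 0.53. A reader might infer that useful tests will be discarded because of this, but the article plans no such step.

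The error lies in two stated objectives and the matching expected results. Allocation, sample size and the comparison of the arms are untouched.

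**What to change.** In section 1 (last paragraph) and section 3, delete the aim to define PFF and the aim to correlate the tests with the diagnosis for the sake of accurate diagnosis. Replace them with wording such as: to describe the clinical tests that are not entry criteria, and the associations among tests and with severity, in children who already meet the entry criteria; these associations are conditional on entry and are expected to be weaker than in unselected children.

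The cost is a wording change in two sections, with no change to procedures, sample size or the randomized analysis.

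Keeping the data of children who are examined and fail a criterion is an option, not a requirement, and it is not free. It needs consent for children who are not enrolled, and the full set of tests completed in them even after one criterion has failed; section 2.3 describes collecting the variables only after agreement to take part. It would bring in children outside the entry limits, but would still supply no independent reference standard, so it would not by itself restore the diagnostic aim.
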